## Materials and methods

### Aim

The aim of this study is to contrast passive and active conditions using peripheral targets in MIB. In the active condition—after the participant reports the initial disappearance (fading from awareness) of the stimulus—they will be cued to saccade to the previously observed location of the target. This saccade is considered as a manifestation of overt active inference. In the passive condition, following a reported disappearance, the sensory consequences of the saccade are ‘replayed’ by moving the stimulus array (which includes the grid), while central fixation is maintained. Passive replay will be based on eye movement trajectories recorded via eye tracking during the active condition, thereby ensuring that visual stimulation is identical across conditions. In each condition, participants will be instructed to indicate—via button press—when the target reappears in consciousness (see Fig 1).

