### Data collection procedures

**1. Behavioural Data.** Participants will use a key press to indicate the disappearance of the peripheral targets. A timestamp will be set when the disappearance response is given, when the cue is initiated, and when the stimuli are actively or passively foveated. This will allow precise extraction of replay gaze trajectories from the onset of fixation. In Experiment A, participants will be required to press the spacebar as soon as they become aware of the stimulus; in Experiment B, participants will be asked to give a forced binary choice after the trial to report whether stimulus reappeared. The invisible boundary that initiates the mask will be expanded if they report reappearance and contracted if they do not. If a reappearance is reported participants will be asked a subsequent question about the identity of the stimulus. The participant can choose a present identity or a ‘no match’ option. In 50% of the trials the identity shown in the trial will not match that presented in this post-trial question, allowing us to compute signal detection theoretic measures. Participant choice will also yield a confidence measure based on their click location (see Fig 3). To analyse the data we will fit linear mixed-effects models on the psychophysical awareness threshold. This will be quantified as the invisible boundary radius at which there is a 50% reappearance report rate under the model, with Active vs. Passive condition included as a predictor, potentially including and potential nuisance variables as covariates. Similar models will be fit to analyse signal detection theoretic measures of target discrimination and decision confidence.

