**Fig 3 pone.0328836.g003:**
[figure not shown]
An example resolved LMM analysis decision tree for experiment A & B. Here solid lines denote variables to be considered and grey boxes (dotted lines) denote decision criteria. Note: 1) Crossed out options are for example only, all options are available in real analysis tree. 2) For display purposes only included variables are written in full but variable selection at each level includes the same forks. 3) The third level criteria uses ascending steps to decide model variable inclusion. 4) Top of the tree denotes the basic model.

Trials will be rejected if:

1)any button press response is made < 3 seconds following the start of the trial2)time to reappearance is reported < 250 ms following the cue.3)time to reappearance is reported > 1 second following the cue.

**2. Eye-tracking.** Binocular gaze and pupillary response data for the experiment will be sampled at a frequency of 1000 Hz using a desk mounted SR Research Eyelink 1000 system (35 mm lens). Testing will be conducted in a sound attenuated room and display luminance will be matched across recording sites (Melbourne and Jena) using luminance measures taken from the four screen quadrants, taking into account room lighting. Participants will be seated with their head stabilised on a chin rest mounted 105.3 cm from the stimulus presentation screen and ~55 cm from the eye-tracking camera to the eye. At the start of the experiment a nine-point calibration and nine-point validation will be conducted. An additional validation will be performed at the start of each block. If any inter-block validation is not considered ‘good’ (worst point error < 1.5°, average error < 1.0°), the initial calibration and block validation will be repeated.

***Passive condition, eye-movement replay.*** The replay data processing must be completed within the inter-block period and has therefore been kept relatively streamlined to prevent additional computation time:

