1)Replay periods are epoched using a window extending from the initialization of the cue to the first fixation on the target stimulus.2)Any values outside of the boundaries of the screen are removed, and eyeblink periods must be linearly interpolated between points in order to maintain a smooth replay. Any datapoint more than 1.5° of visual angle away from the linear path from fixation to target will not be considered in the replay. Any datapoint more than 1.5° away from the previous data point is considered an error and will not be considered in the replay.3)Any trials containing poor signals (i.e., missing more than 20% of sample points in both eyes; [41]) will not be selected for replay. For replays that meet this standard all non-included samples will be linearly interpolated. To ensure equal numbers of active and passive trials, active trials may be used in replays additional times after running through all available replays. The replay path corresponding with the target stimuli will be used for replay if available, but the path trajectory will be transformed across randomly selected polar angles.

***Analysis.*** The following pre-processing steps describe the post-experiment analysis of eye tracking data for use in trial validation, eye-blink, microsaccade and pupillometry measures:

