### Operational hypotheses

The hypotheses being tested by the experiments described in this Study Protocol are as follows:

Experiment A: changes in conscious experience manifest earlier in the active than the passive condition, as measured by behavioural responses;

Experiment B: backward masking can preclude changes in conscious experience in the passive condition but not (as much) in the active condition.

These hypotheses stem from the putative role of active inference to confirm the sensory input expected following action (as described in the Introduction). Active sampling should promote faster resolution of uncertainty, engendering earlier perceptual inference. These hypotheses can be expressed in terms of the following predictions about the patterns of data we expect to observe in each experiment:

1]*Subjective report of reappearance of peripheral stimuli will occur after a shorter delay following subjective disappearance in the active vs. the passive condition of Experiment A* (see Table 1).2]*The psychophysical reappearance threshold for the radius of the masking boundary (once eye gaze is inside this invisible circular boundary the stimulus is masked) will be higher ; i.e., a larger radius in the active vs. the passive condition of Experiment B* (see Table 2).

**Table 1 pone.0328836.t001:** Predictions about the effect of active (vs. passive) sampling on target time-to-reappearance in Experiment A.

Theory	Decrease	No change	Increase	Confidence
IIT	X	X		Low
NREP	X	X		Medium
AI	X			High

**Table 2 pone.0328836.t002:** Predictions about the effect of active (vs. passive) sampling on mask onset boundary distance in Experiment B.

Theory	Decrease	No change	Increase	Confidence
IIT		X	X	Low
NREP		X	X	Medium
AI			X	High

Each of the other theories considered in the adversarial collaboration, IIT and NREP, offer different predictions to these, which also differ in their degree of confidence:

IIT is consistent with both manipulations (active or passive target sampling) quickly breaking suppression, by changing visual cortex state. Motor involvement (active) may be enough to tip the balance towards breaking suppression more easily, for a small difference in time to reappearance and/or masking boundary. Thus, for Experiment A (see Table 1), IIT predicts either decrease or no change, with low confidence; for Experiment B (see Table 2), IIT predicts either increase or no change, with low confidence.

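### The Experiment A replay is cut from cue initiation with no stated correction for display delay, so passive targets may arrive late by that delay, in the direction that supports AI-C

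*Protocol article*

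**What the plan says.** All references are to the protocol article.

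- **Replay window** (Data collection procedures, Passive condition, eye-movement replay, step 1): "Replay periods are epoched using a window extending from the initialization of the cue to the first fixation on the target stimulus". The other replay steps deal with off-screen samples, blinks, path deviation, missing samples, interpolation and rotation to a new polar angle. None deals with timing.
- **Timestamps** (Data collection procedures, Behavioural Data): "A timestamp will be set when the disappearance response is given, when the cue is initiated, and when the stimuli are actively or passively foveated". The text does not say whether these are software times or measured light onsets. The next sentence gives a different anchor for the replay: "This will allow precise extraction of replay gaze trajectories from the onset of fixation".
- **Outcome limits** (trial rejection list after Fig 3): trials are dropped if "time to reappearance is reported < 250 ms following the cue" or if "time to reappearance is reported > 1 second following the cue". Prediction 1 under Operational hypotheses counts instead from subjective disappearance.
- **Claim of equality** (Aim): the replay is based on recorded eye movements, "thereby ensuring that visual stimulation is identical across conditions".
- **Decision rule** (Current study): no difference, or longer blindness in the active condition, is strong evidence against AI-C; longer blindness in the passive condition mainly supports it.

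Gaze is sampled at 1000 Hz. The article gives no display delay or refresh rate, and describes no check of when the replayed target physically arrives.

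**The concern.** The active condition depends on the display once: the cue must light up before the participant can react to it. After that the eye moves and the target stays still. The passive condition depends on it twice, because the recorded path includes the wait for the active cue to light up and is then drawn on a screen with the same delay. Followed literally, the stated anchor makes the passive target late by one display delay on every passive trial.

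Experiment A is a test of zero against positive, and AI-C is the only one of the three theories whose prediction in Table 1 excludes no change. A constant technical lag in passive trials could turn a null that counts against AI-C into a result that counts for it. More trials or participants would not average it out. A second laboratory using the same scripts and setup could reproduce it.

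**Working it through.** **1. The plan's own figure.** The article adopts 55 participants for at least 80% power at partial eta squared .13. Two-sided alpha of 0.05 is assumed, as none is stated.

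- f² = 0.13 / (1 − 0.13) = 0.1494, so the standardised paired difference dz = √0.1494 = 0.387.
- The paired t-test (noncentral t, df 54) has power 0.804 at n = 55 and 0.796 at n = 54. The figure reproduces.

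**2. Timeline.** Let L be the command-to-light delay, R the saccade latency and D the saccade duration. Times run from the recorded cue time, taken as the software command.

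- Active: the cue lights at L and the eye reaches the target at L + R + D. The recorded path has this length.
- Passive: the arrival frame is commanded at L + R + D and lights at 2L + R + D.
- Excess: (2L + R + D) − (L + R + D) = L.

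The whole path is shifted by L, so the excess does not depend on where along the path the target reappears, provided the report is driven by the moved stimulus.

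**3. Variants.**

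- Timestamp synchronised to the frame flip but not to light: the same algebra applies, with L replaced by the remaining panel delay.
- Epoch cut from cue light onset, with its first sample drawn on the passive cue's frame: recorded length R + D, light at L + R + D, excess 0.
- Each 1000 Hz sample waits for the next frame: add about half a frame on average, 8.3 ms at 60 Hz or 3.5 ms at 144 Hz (assumed rates). Drawing to the nearest frame adds no mean shift.

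**4. Does the outcome clock matter?** A cue delay inside the clock is the same in both conditions and cancels. The interval from disappearance report to cue is jittered in the same way in both. Counting from the cue or from disappearance therefore leaves the same excess L. Counting from foveation also leaves it if the passive foveation stamp is a software time.

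**5. Size.** The SD s of participants' mean passive-minus-active differences is not given; 40 to 100 ms is assumed. The detectable effect is 0.387 × s:

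- s = 40 ms: 15.5 ms
- s = 100 ms: 38.7 ms

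The chance of a significant result in the predicted direction with no true effect comes from the noncentral t with df 54 and noncentrality (L/s)√55. The nominal rate is 2.5%.

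| Excess | s = 40 | s = 60 | s = 80 | s = 100 |
|---|---|---|---|---|
| 5 ms | 14.7% | 8.8% | 6.6% | 5.5% |
| 10 ms | 44.5% | 22.8% | 14.7% | 10.9% |
| 16.7 ms | 86.0% | 52.7% | 33.0% | 22.9% |
| 25 ms | 99.5% | 85.9% | 62.4% | 44.5% |

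An excess of 25 ms equals or exceeds the detectable effect when s is at most 25 / 0.387 ≈ 65 ms.

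**6. Effect of the 250 ms and 1 s limits.** Assuming normally distributed times, a 16.7 ms shift appears as 15.2 ms (mean 600, SD 150 ms) or 9.9 ms (mean 800, SD 200 ms). The limits shrink the shift but do not reverse it.

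**The case against.** The strongest reply is that the article never says cue times are software commands. Initiation could mean a measured onset, and frame timing is the kind of detail a condensed article leaves to the scripts, which the Data management and sharing plan promises to release. The listed replay steps concern data processing and need not be a full account of presentation timing. This stands to the extent that the point must be conditional: a reader might infer that every passive trial is certainly late, and the document does not show that. It does not dispose of the point. The article fixes an anchor and asserts identical stimulation on the strength of it, and even a frame-synchronised timestamp leaves the panel delay counted twice.

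Other inferences a reader might draw are not supported:

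- **The cue-based clock creates the bias.** It does not; a cue delay there cancels (working, step 4).
- **Arrival is not recorded.** Foveation is timestamped in both conditions. What is missing is a statement that the passive stamp is light onset, or that it enters the outcome.
- **The bias differs between sites.** The participants section says the setups and scripts are identical, so a shared bias is at least as likely.
- **Half a frame always remains.** That depends on how samples are assigned to frames.

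It is also fair to say that the planned analysis is a mixed or generalised linear model, so the paired-t rates are only a guide. But a delay confined to passive trials goes into the condition contrast under any such model, and the planned covariates do not include physical arrival time.

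**Conclusion.** The concern holds in conditional form. If cue and replay times are not measured light onsets and the replay is not already advanced, passive reappearance in Experiment A is late by the display delay L, plus up to about half a frame if samples wait for the next frame. The error favours AI-C, and stimulation is then not identical across conditions.

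Its size cannot be settled from the document, because L, the refresh rate and the SD of within-person differences are all absent. With L of 5 to 25 ms and an SD of 40 to 100 ms, both assumed, it ranges from negligible to as large as the effect the sample size was chosen to detect. The higher error rates belong to long delays combined with small SDs and should not be read as expected values. The figures also assume that reports shift one for one with target arrival.

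The article words the replay anchor in two ways, cue initiation and onset of fixation, and these need reconciling in any case.

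**What to change.** 1. State whether cue, replay and foveation times are software times or measured light onsets.
2. Bench-measure the command-to-light delay on the setup at each site, and report it with the refresh rate.
3. For remaining sessions, start the replay epoch at cue light onset, with its first sample on the passive cue's frame, or advance the replay by the measured delay by trimming the static part before the saccade. Do one or the other, not both. Then check that physical arrival times match across conditions, which also shows any frame-rounding residue.
4. For trials already run (the article says data collection is underway), subtract the measured constant from passive times before applying the 250 ms and 1 s limits. Alternatively, time both conditions from the recorded foveation event, with the passive stamp corrected to light onset.
5. Reconcile the replay anchor in the Behavioural Data paragraph with step 1 of the replay procedure.

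The cost is one bench measurement per site, one constant in the replay script and one line in the analysis. No participants are added. The estimated active-passive difference may become slightly smaller.

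### The replay quality limit is counted over the whole cue-to-fixation window, so a replay can pass with its eye movement largely or wholly interpolated

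*Protocol article*

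**What the plan says.** The rules are in the Protocol article under Data collection procedures, 2. Eye-tracking, Passive condition, eye-movement replay.

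- Step 1 sets the window: "Replay periods are epoched using a window extending from the initialization of the cue to the first fixation on the target stimulus".
- Step 2 deals with blinks: "eyeblink periods must be linearly interpolated between points in order to maintain a smooth replay". It also drops off-screen values and applies two filters: "Any datapoint more than 1.5° of visual angle away from the linear path from fixation to target will not be considered in the replay", and "Any datapoint more than 1.5° away from the previous data point is considered an error and will not be considered in the replay".
- Step 3 sets the quality bar: "Any trials containing poor signals (i.e., missing more than 20% of sample points in both eyes; [41]) will not be selected for replay". It continues: "For replays that meet this standard all non-included samples will be linearly interpolated".

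The Aim section says passive replay is based on the recorded trajectories, "thereby ensuring that visual stimulation is identical across conditions". Current study, in the Introduction, makes the same claim for visual input and retinal activation, and the Main experiment text of Experiment A calls the replay exact.

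**The concern.** The part of the window that defines the stimulus is the short movement. The quality limit is spread over that movement plus the still period before it, so good data while the eye is at rest can offset having no data while it moves. The missing movement is then drawn as a straight line at constant speed.

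Blinks raise a second issue. They are filled in step 2, before the count in step 3, and the text does not say whether filled samples still count. During a blink in the active trial the lids were closed. In the passive replay the same interval becomes a visible sweep of the array.

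Interpolation alters only the passive stimulus. Where it replaces the movement, an active–passive difference, or its absence, could partly reflect a different stimulus and not the absence of action. In Experiment B the target is removed when the boundary meets gaze, and the boundary radius at threshold is the outcome. A changed trajectory therefore changes exposure before masking at a given radius.

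**Working it through.** The plan gives no figure of its own here to reproduce.

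**Inputs from the document:** replay window and 20% limit (steps 1 and 3); 1000 Hz sampling, so one sample is 1 ms (2. Eye-tracking); target at 9 degrees (Experiment A, Design); filters of 1.5 degrees (step 2); minimum trial length 4 s (Experiment A, Main experiment).

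**Assumptions not in the document:** movement time D = 30–60 ms, latency L = 100–300 ms, blink length B = 100–200 ms, and a smooth minimum-jerk profile for the true movement.

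**1. When can the whole movement be missing?** Its share of the window is D/(L+D). It passes when D/(L+D) ≤ 0.20, i.e. L ≥ 4D.

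| D | Minimum L | Share at L=100 | L=200 | L=250 | L=300 |
|---|---|---|---|---|---|
| 30 ms | 120 ms | 23.1% | 13.0% | 10.7% | 9.1% |
| 40 ms | 160 ms | 28.6% | 16.7% | 13.8% | 11.8% |
| 50 ms | 200 ms | 33.3% | 20.0% | 16.7% | 14.3% |
| 60 ms | 240 ms | 37.5% | 23.1% | 19.4% | 16.7% |

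None passes at 100 ms. All pass at 250 and 300 ms. If step 3 means the whole trial and not the replay window, the allowance is at least 0.20 × 4 s = 800 ms, which is looser still.

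**2. Do the 1.5-degree filters prevent this?** No. A ramp of 9 degrees over 40–80 ms moves 9/40 = 0.23 to 9/80 = 0.11 degrees per sample, along the straight path, so it triggers neither filter. Nor can the off-path filter create a whole-movement gap by itself. A sample within 1.5 degrees of fixation or target is within 1.5 degrees of the line joining them, so the filter can remove only the middle of a flight that starts at fixation and lands near the target. Whole-movement loss needs dropout or a blink.

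**3. Blinks.** If blink samples count as missing, a blink passes when B/W ≤ 0.20, where W is the window, i.e. W ≥ 5B: 500 ms for B = 100 ms and 1000 ms for B = 200 ms. A 100 ms blink takes 40% of a 250 ms window and 25% of a 400 ms window (both fail), and 16.7% of 600 ms (passes). If filled samples do not count, a blink of any length passes.

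**4. Size of the distortion.** If the gap exactly covers the movement, the ramp differs from the assumed true path by at most about 1.3 degrees. If the gap is the largest allowed and ends at landing, with D = 40 ms:

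| Window | Gap (20%) | Ramp speed | Peak position error |
|---|---|---|---|
| 250 ms | 50 ms | 9/0.050 = 180 deg/s | 2.7 degrees |
| 300 ms | 60 ms | 9/0.060 = 150 deg/s | 3.7 degrees |
| 400 ms | 80 ms | 9/0.080 = 112 deg/s | 4.9 degrees |

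A true 40 ms movement averages 9/0.040 = 225 deg/s. In these cases the array also starts to move before the eye did.

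**5. Do later rules catch it?** The post-experiment filter (Analysis, step 5) removes trials missing more than 30% of samples. It is looser, also ignores where gaps fall, and does not refer to the quality of the replay shown. Accepted replays carry over between passive blocks and may be reused, so one poor replay can recur.

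**The case against.** The strongest reply is that this is only a possibility. Every duration above is assumed, and dropout must fall on a few tens of milliseconds of flight while total loss stays within 20%. That stands. A reader might infer that many replays are synthetic, but the document gives no basis for any frequency.

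Four further objections stand in part:

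- The any-length blink problem depends on filled samples not being counted. The closing sentence of step 3 suggests that filling follows the check, while step 2 places blink filling before it. The text does not settle this.
- The bar refers to both eyes and recording is binocular, so one good eye may supply the path. The steps do not say which eye drives the replay.
- When the gap just covers the movement, the error of about 1.3 degrees is below the 1.5-degree path tolerance and the 1.5-degree worst-point validation limit. Timing and speed still differ, and larger gaps do more.
- The protocol openly says that replay processing was kept simple because it must finish between blocks, and the code will be shared. That explains the rule but does not reconcile it with a claim of identical stimulation. The rule is stated in the article itself.

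Barring every source trial with a blink anywhere between cue and fixation would be broader than needed. It would also make replay sources a selected subset of the active trials analysed.

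**Conclusion.** The point holds as a loophole in the stated rule. With movement times of 30–60 ms and latencies of at least 120–240 ms respectively, a source trial with no measured sample during the movement meets the 20% limit. A blink across the movement can also pass, at any length or only in long windows depending on an unstated counting rule. For such replays the claim of identical stimulation fails, with a position error from about 1.3 degrees up to 4.9 degrees in the cases worked.

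Two stronger readings are not supported: that the off-path filter can strip out the whole flight, and that the active–passive contrast is biased in a known direction or by a known amount. Neither the frequency nor the effect on time to reappearance or on the masking threshold can be derived from the document. The change is worth making because identical stimulation is the design's central control and the correction is cheap.

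**What to change.** In step 3 of the replay procedure:

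1. Count blink, off-screen and discarded samples as missing before any interpolation.
2. Keep the 20% limit on the whole window, and apply it also to the samples between movement onset and landing, using the eye that drives the replay.
3. Do not select for replay a source trial whose blink overlaps the movement.
4. Record the interpolated share of each replay's movement. Repeat the active–passive comparison without affected passive trials and their source active trials, so that the two conditions stay matched.

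Item 4 also covers trials already run, since Status and timeline says data collection is underway. The cost is a few lines in the inter-block script, including detection of movement onset. There will be fewer eligible source trials and more reuse of accepted replays, which step 3 already allows.
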